## Abstract

**Background:**

Women with cancer are significantly more likely to fall than women without cancer placing them at higher risk of fall-related fractures, other injuries and disability. Currently, no evidence-based fall prevention strategies exist that specifically target female cancer survivors. The purpose of the GET FIT (Group Exercise Training for Functional Improvement after Treatment) trial is to compare the efficacy of two distinct types of exercise, tai chi versus strength training, to prevent falls in women who have completed treatment for cancer. The specific aims of this study are to: 1) Determine and compare the efficacy of both tai chi training and strength training to reduce falls in older female cancer survivors, 2) Determine the mechanism(s) by which tai chi and strength training each reduces falls and, 3) Determine whether or not the benefits of each intervention last after structured training stops.

**Methods/Design:**

We will conduct a three-group, single-blind, parallel design, randomized controlled trial in women, aged 50–75 years old, who have completed chemotherapy for cancer comparing 1) tai chi 2) strength training and 3) a placebo control group of seated stretching exercise. Women will participate in supervised study programs twice per week for six months and will be followed for an additional six months after formal training stops. The primary outcome in this study is falls, which will be prospectively tracked by monthly self-report. Secondary outcomes are maximal leg strength measured by isokinetic dynamometry, postural stability measured by computerized dynamic posturography and physical function measured by the Physical Performance Battery, all measured at baseline, 3, 6 and 12 months. The sample for this trial (N=429, assuming 25% attrition) will provide adequate statistical power to detect at least a 47% reduction in the fall rate over 1 year by being in either of the 2 exercise groups versus the control group.

**Discussion:**

The GET FIT trial will provide important new knowledge about preventing falls using accessible and implementable exercise interventions for women following chemotherapy for cancer. ClinicalTrials.gov NCT01635413

## Background

Women diagnosed with cancer have a favorable prognosis in terms of survival [1], but will likely face treatment-related side effects and symptoms that threaten quality of life. One of the serious after effects of cancer treatment is an increased risk of falling. Women who have had cancer are significantly more likely to fall than women who have not [2-4] and falls are associated with serious injuries, including fractures [5]. Chen et al. reported an elevated risk of falls after women developed breast or other cancers compared to women never diagnosed with cancer (HR = 1.15, 95%CI: 1.06-1.25 and HR = 1.27, 95%CI: 1.18-1.36 for breast cancer and other cancers, respectively) [6]. In these cancer survivors, hip fracture risk was doubled after diagnosis and multiple fallers (≥2 falls in a year) were significantly more likely to break their hips (HR = 2.05, 95%CI: 1.82, 2.31) or spines (HR = 1.76, 95%CI; 1.58, 1.95) compared to women who fell once or not at all [2]. Since falls increase *after* women are diagnosed with cancer [2], the disease and/or treatments are likely to be the cause of increased falls. Cancer treatment can cause muscle wasting [7-11], peripheral neuropathy in the feet [12] and vestibular ototoxicity [13,14]. and these same problems have been linked to poor balance and falls in older adults [15-17] and persons with diabetes [18-20]. Reduced physical activity, common during and after chemotherapy [19], could further contribute to fall risk because inactivity leads to declines in neuromuscular function.

Although the precise reasons that falls increase after cancer diagnosis remain to be determined, exercise is a fall prevention strategy that has demonstrated efficacy in older adults [20,21] and might also be effective in cancer survivors. In older adults, both strength training and tai chi are types of programs that effectively reduce falls because they each address the underlying reasons people fall in old age, e.g., muscle weakness and poor balance [22-24]. The specific ways that cancer treatment changes fall risk factors suggest that strength training or tai chi might prevent falls in female cancer survivors through different mechanisms. Strength training can prevent falls because strong muscles promote stability that prevents the initiation of a fall [16], and counteracts the downward force of a fall once balance is lost [25]. There is strong evidence that strength training reduces falls by 30%-50% in older adults without cancer [17,24,26-32]. In contrast to strength training, tai chi another standing exercise consisting of a series of individual dance-like movements linked in a continuous sequence, flowing slowly and smoothly from one movement to another that emphasizes weight transfer and movement of the body outside of its base of support [33]. By doing so, it improves postural control and balance [34] that can prevent falls. A recent meta-analysis that pooled the effect of six controlled trials examining the efficacy of exercise to reduce falls in older adults reported a 49% reduction in fall incidence from tai chi (Incidence Rate Ratio (IRR)=0.51, 95% CI: 0.38–0.68) [35]. Falls in BCS have been seldom studied and exercise has only been explored by a singular trial that considered falls as a secondary endpoint [36]. This study failed to find that strength training protected against falls; however, the study did not use a strength training program designed for fall prevention and the study was not powered for falls.

The specific ways that cancer treatment changes fall risk factors suggest that strength training or tai chi may differentially reduce falls in female cancer survivors or may be equally effective in preventing falls. While either strategy reduces falls in older adults, neither has been rigorously tested in cancer survivors. The objective of the GET FIT (Group Exercise Training for Functional Improvement after Treatment) trial is to compare the efficacy of 2 distinct types of exercise, tai chi versus strength training, to prevent falls in women who have completed treatment for cancer. To our knowledge, this study will be the first to test the efficacy of any intervention in cancer survivors with falls as a primary endpoint, to identify the mechanisms through which either intervention reduces falls, and to evaluate whether intervention benefits on falls persist long-term. The primary aim of our study is to determine and compare the efficacy of tai chi training and strength training to reduce falls in older female cancer survivors, with a secondary aim to determine the mechanism(s) by which tai chi and strength training each reduce the risk of falls and, a tertiary aim to determine how well the benefits of each intervention persist long-term. The purpose of this paper is to describe the study protocol for the GET FIT trial and present potential challenges during the study and our approach to dealing with these challenges.

## Methods/Design

### Study design and setting

The study is a single-blind, parallel group, randomized controlled trial comparing 3 groups: 1) tai chi, 2) strength training, and 3) a placebo control. The study period is 12 months including a 6-month supervised intervention and a 6-month follow-up with the primary outcome measured monthly and secondary and process outcomes measured at baseline, 3, 6 and 12 months. The primary site for conduct of the study, including all study visits, is Oregon Health & Science University (OHSU) in Portland, Oregon. Exercise training will be conducted at OHSU and additional community locations serving the outer Portland area. The OHSU IRB has approved the protocol and informed consent for the study. The trial is registered with ClinicalTrials.gov NCT01635413.

### Sample

Participants are underactive women aged 50–75 years who completed chemotherapy for cancers without neurologic involvement. The eligibility criteria are inclusive to demonstrate the feasibility of the intervention in a broad range of female cancer survivors and to enhance the generalizability of the findings. Women with chronic conditions and health problems are eligible unless the problems are serious enough to preclude participation in moderate level exercise. To be eligible to participate in the study women must meet the following inclusion criteria: 1) diagnosed with stage I-IIIc cancer other than cancers of the brain or spinal cord, 2) completed chemotherapy >3 months prior to enrollment and no concurrent adjuvant therapy other than hormone manipulation therapy for breast cancer, 3) aged 50–75 on date of enrollment, 4) currently underactive (<60 minutes of moderate intensity exercise per week in the last month; 5) cognitive ability sufficient to answer survey questions, participate in the exercise classes and performance tests, and provide informed consent and 6) free of any medical condition, movement or neurological disorder, or medication use that contraindicates participation in moderate intensity exercise.

### Power and sample size

The sample size is powered to address the primary study aim to reduce falls. In older adults, 30% of community-dwelling elders are likely to fall within 1 year [37] and Li and others have reported a reduction in fall risk of 47% from 3 [38] or 6 [22] months of tai chi exercise. This effect size provided a realistic estimate of the expected reduction in fall risk and was used as the basis for power analyses. The required sample to test the primary hypotheses in a negative binomial regression model [39] was determined with the following assumptions:, alpha=.05, 25% shared variance (R [2]=.25) among the dummy vectors representing treatment, and an overdispersion parameter (Phi) of 2.5. Under these assumptions a sample size of n=342 (n=114 per group) will provide 80% power to detect at least a 47% reduction in the fall rate over 1 year by being in the 2 experimental groups (tai chi and strength training) versus the control group. These estimates were generated using PASS 2008 [40]. To protect against an estimated attrition of 25% during the intervention period, 143 participants will be randomized per group (total sample size: N=429). The attrition estimate is based on attrition rates in yearlong studies of weighted vest strength training in BCS [41] and slightly higher than what has been observed in 1-year studies of older women without cancer participating in tai chi exercise [42,43] (19%-24%) or resistance exercise (24%) [43].

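### The 80% power at n=342 needs about 1.0 fall per woman-year in the control group, a rate the article does not state and its only event figure (30% fallers in a year) does not support

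*Protocol article*

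**What the plan says.** All of this stands in the protocol article under Power and sample size.

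- The paragraph opens with a proportion of people: "In older adults, 30% of community-dwelling elders are likely to fall within 1 year".
- It then cites tai chi studies that "have reported a reduction in fall risk of 47" percent. That is a reduction in risk, and it is taken as the effect size.
- The model is a negative binomial regression. Besides alpha, the listed assumptions include "25% shared variance (R [2]=.25) among the dummy vectors representing treatment". For the spread of the counts, the article assumes "an overdispersion parameter (Phi) of 2.5".
- The resulting claim is that "a sample size of n=342 (n=114 per group) will provide 80% power". The effect in view is described as "at least a 47% reduction in the fall rate over 1 year".
- The source of the figures is given as "These estimates were generated using PASS 2008".

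No number of falls per woman-year in the control group appears there or elsewhere in the article. The Background gives only relative figures: hazard ratios for falls after cancer of 1.15 (breast) and 1.27 (other cancers), and relative reductions with exercise.

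**The concern.** In a count model, power depends on the expected number of falls, so the control rate is as important an input as the rate ratio. The paragraph moves from the share of people who fall at least once to a reduction in the rate of falls without the link between them. With overdispersion the two can differ widely, because a few women fall repeatedly.

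A reader who takes the 30% as the event basis cannot get to 342. At stake is the main justification of the trial's size, which the Abstract repeats as a claim of adequate power.

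**Working it through.** **Inputs from the article.** IRR = 1 − 0.47 = 0.53; alpha .05; power 80%; Phi = 2.5; R² = .25; three equal groups; one year of exposure.

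**Assumptions of this check.** Alpha is two-sided. The formula is the Signorini-type one for Poisson-type regression with overdispersion. The tested dummy covers π = 1/3 of the sample. The last is well supported: two dummies for three equal groups correlate at −0.5, and (−0.5)² = .25, the stated R².

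**Formula.** With λ the control rate per woman-year,

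N = Phi × [z(.975)√V0 + z(.80)√V1]² / [λ × (ln IRR)² × (1 − R²)]

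- V0 = 1/[π(1 − π)] = 4.5
- V1 = 1/(1 − π) + 1/(π × 0.53) = 1.5 + 5.660 = 7.160
- Bracket: 1.960 × 2.1213 + 0.8416 × 2.6759 = 4.158 + 2.252 = 6.410; squared, 41.09
- (ln 0.53)² = 0.4031
- N = 2.5 × 41.09 / (λ × 0.4031 × 0.75) = 339.8/λ

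**Reproducing 342.** λ = 1.0 gives 339.8, which rounds up to 114 per group, or 342. Solving for exactly 342 gives λ = 0.993. The match makes a rate of about 1.0 a plausible input, but it is inferred.

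**Share of fallers at that rate.** Phi is not defined, so both usual readings were taken.

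- Variance = Phi × mean: P(no fall) = 2.5^(−λ/1.5). At λ = 1.0 this is 0.543, so 46% fall.
- Variance = mean + Phi × mean²: P(no fall) = (1 + 2.5λ)^(−0.4). At λ = 1.0 this is 0.606, so 39% fall.

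**Rate implied by 30% fallers.** Setting P(no fall) = 0.70:

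- First reading: λ = −1.5 × ln 0.70 / ln 2.5 = 0.584, and N = 582.
- Second reading: λ = (0.70^(−2.5) − 1)/2.5 = 0.576, and N = 590.

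**Power at 342.** z(power) = {√[342 × λ × 0.4031 × 0.75/2.5] − 4.158}/2.676. At λ = 0.584 this is (4.914 − 4.158)/2.676 = 0.283, or 61%. At 0.576 it is also 61%.

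| Control rate per woman-year | Power at 342, 1 year |
|---|---|
| 0.58 (30% fallers) | 61% |
| 0.6 | 62% |
| 0.8 | 72% |
| 1.0 | 80% |

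**Allowing for higher risk in survivors.** Applying the Background hazard ratios to the 30%, fallers = 1 − 0.70^HR.

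- HR 1.15: 33.6% fallers, λ = 0.67 to 0.72, power 66% to 68%.
- HR 1.27: 36.4% fallers, λ = 0.74 to 0.84, power 70% to 74%.

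**Other settings.** Keeping Phi = 2.5 and R² = .25 but trying one- and two-sided alpha and π of 1/3, 1/2 and 2/3, the lowest control rate that gives 342 is 0.68 (one-sided, π = 1/2). This is still above 0.58.

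**The case against.** The strongest reply is that this is an unstated input in a condensed article. The 30% is background: it is not among the listed assumptions, and the sentence on the basis for the power analysis refers to the 47% reduction. The software needs a control rate, the full protocol may give it, and 342 does reproduce with every listed assumption and a rate of 1.0, so no arithmetic slip is shown. Women after cancer also fall more than the elders behind the 30%.

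Much of this stands. The article does not say that 30% was entered, the rate of 1.0 is an inference under an assumed formula, and the hazard ratios narrow the gap. They do not close it: even multiplying the 30% directly by 1.27 (38.1% fallers, λ at most 0.93) gives at most 78%. Nor is this only an omission. The article lists its assumptions, says the sample size follows from them, and gives one event figure, which points to a materially lower rate than the result needs.

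A reader might infer more than the article supports:

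- **That the trial is underpowered.** The true fall rate in these women is unknown. The 30% describes elders in general, whereas the sample is women aged 50 to 75 after chemotherapy, and the difference could act in either direction.
- **That 30% is a rate of 0.30.** That gives N = 1,133 and 41% power, but it treats a proportion of fallers as a rate of falls, so it does not measure the gap.
- **That a rate of 0.30 was entered.** With Phi = 1 and R² = 0 it also returns 339.8, but this contradicts the stated Phi and R².

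The primary analysis covers six months while the power statement covers one year. That is a separate matter, and none of the figures here rely on it.

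**Conclusion.** The point holds: the stated 80% power is not supported by the basis shown. The sample of 342 needs about 1.0 fall per control woman-year (39% to 46% fallers), whereas 30% fallers corresponds to about 0.58. At that rate the same formula gives about 61% power, or roughly 66% to 74% after scaling by the article's hazard ratios.

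This rests on two-sided alpha, one third of the sample per arm, the assumed formula, and Phi read in one of its two usual senses. Power figures from another method would differ somewhat; simulated negative binomial regression with 114 per group gave 53% to 56% at 0.58. The conclusion concerns the justification of the sample size. It is not a finding that power will in fact fall short.

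**What to change.** Under Power and sample size:

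1. State the control fall rate entered, in falls per woman-year, and its source.
2. Keep that rate separate from the 30% who fall at least once.
3. Define Phi.
4. Give the power at 342 as conditional on the control rate. By the formula above, over one year, it is about 62% at 0.6, 72% at 0.8 and 80% at 1.0; the sponsor should confirm these with its own software.
5. If 30% fallers is the intended basis, lower the 80% claim accordingly, here and in the Abstract. If a rate near 1.0 was intended, justify it for this population.

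A flat replacement of 80% by a single lower figure is not warranted, because the true rate is unknown. The cost is one rerun and a reworded paragraph. The downside is that the stated power may look less favourable.

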## Measures

### Primary outcome

Falls: In this study, a fall is defined as unintentionally coming to rest on the ground or at some other lower level, not as a result of a major intrinsic event (e.g., stroke or syncope) or overwhelming hazard [57]. Falls will be assessed retrospectively at baseline through 6-month recall to characterize the sample and check for equality of randomization. Falls will be assessed prospectively during the study by monthly reports completed through a web portal or returned by postal and/or electronic mail, methods proven successful in our 2 previous studies and by others, including [name] [3,4,22,58]. In our recently completed observation study of BCS (N=58), we obtained 98% of monthly fall reports over 6 months [3]. If a participant indicates a fall she will then be asked to detail any injury that resulted from each fall. A fall will be considered “injurious” if it results in fractures, head injuries, sprains, bruises, scrapes, or serious joint injuries, or if the participant seeks medical care [57]. Of interest in the study are the number of falls, the number of injurious falls, and medical care resulting from a fall during the intervention period.

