### Data analysis plan

The univariate distribution of each variable will be examined to check for departure from normality and outliers [76]. For each analysis described below, each subject will be analyzed according to the group to which she was randomly assigned and regardless of missing data (i.e., intention to treat). Medical treatment changes and cancer recurrence during the study will be tracked and used to describe the sample and document why participants may not have completed the study. In the unlikely event of a large subgroup, these data could be used for exploratory sub-group analysis to suggest directions for future research. Age, cancer type (breast or other), and time since cancer treatment completion, will be included as covariates in all analyses.

A negative binomial regression model will be used to test the efficacy of tai chi and strength training (versus stretching control) in reducing the total number of falls per participant that occur during the intervention period (from baseline to 6 months). Negative binomial regression is preferred over Poisson regression for modeling the count data because of the overdispersion that is common with actual research data [40,77]. Intervention type will be entered into the model as 2 dummy vectors, with the reference group being the control group. Fall rates for participants who drop out of the study will be adjusted by accounting for their exposure time within the study timeframe. A significant incidence rate ratio (IRR) less than 1.0 for the dummy vector representing tai chi and/or strength training would provide support for the hypothesis that the respective intervention reduced the rate of falls compared to the control group (controlling for covariates).

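### The stated 80% power is for the fall rate over 1 year, but the primary efficacy test counts falls only over the 6-month intervention, so it does not have that power

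*Protocol article*

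**What the plan says.** Two places give the power claim, both with a 1-year horizon:

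- Power and sample size: 342 women "will provide 80% power to detect at least a 47% reduction in the fall rate over 1 year".
- Abstract, Methods/Design: the sample gives "adequate statistical power to detect at least a 47% reduction in the fall rate over 1 year".

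Two places define what is tested, both with a 6-month horizon:

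- Data analysis plan: the negative binomial model tests each exercise programme against control in "reducing the total number of falls per participant that occur during the intervention period (from baseline to 6 months").
- Measures, Primary outcome: of interest are "the number of falls, the number of injurious falls, and medical care resulting from a fall during the intervention period".

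Falls are also logged in months 6 to 12 (Six-month follow-up period). In the Data analysis plan these enter only the piecewise model with a change point at 6 months and the model for continued exercise, which serve the third aim. No power figure is given for a 6-month window.

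**The concern.** A rate ratio has no time unit, but the precision with which it is estimated depends on the number of falls observed. If the rate is constant, a 6-month window contains half the falls of a 12-month window. A sample that gives 80% power over a year therefore gives less over the first 6 months.

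The 80% figure justifies the size of a three-arm trial and appears in the abstract. If the primary test is weaker than stated, a null result for either programme could be taken as evidence of no effect when the trial had a substantial chance of missing a 47% reduction.

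**Working it through.** **Inputs from Power and sample size**

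- Rate ratio: 1 − 0.47 = 0.53, because earlier tai chi studies "have reported a reduction in fall risk of 47% from 3 [38] or 6 [22] months of tai chi exercise".
- Alpha 0.05; sidedness is not stated, and two-sided is assumed here.
- R² = 0.25: "25% shared variance (R [2]=.25) among the dummy vectors representing treatment". With three equal groups the correlation between the two treatment dummies is −(1/9)/(2/9) = −0.5, so R² = 0.25. This fits a model with a dummy share p = 1/3.
- Phi: "an overdispersion parameter (Phi) of 2.5".
- N = 342.

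**Input not in the document:** the mean number of falls per control woman. The 30% quoted for older adults is a proportion of people who fall, not a mean count.

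**Formula** (Poisson regression with overdispersion, mean count μ over the window):

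N = Phi × (1.96√V0 + 0.8416√V1)² / [μ × B² × (1 − R²)]

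with V0 = 1/[p(1−p)] = 4.5, V1 = 1/(1−p) + 1/(p × 0.53) = 1.5 + 5.66 = 7.16, and B² = (ln 0.53)² = 0.403.

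Power = Φ{[√(N μ B² (1−R²)/Phi) − 1.96√V0] / √V1}, where Φ is the normal distribution function.

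**Step 1. Reproduce 342.** With μ = 1.0, N = 2.5 × (4.158 + 2.252)² / (0.403 × 0.75) = 339.8, which is 342 when rounded up to three equal groups. Power at 342 is 80.2%. The value 1.0 is back-solved. Some other combinations of rate and sidedness also land near 342, so this is a consistent reading and not proof of what was entered.

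**Step 2. Halve the exposure (μ = 0.5).** Two treatments of Phi:

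- Phi held at 2.5.
- Phi shrinking with the mean. For a negative binomial, Phi = 1 + kμ; 2.5 at μ = 1.0 gives k = 1.5, so Phi = 1.75 at μ = 0.5.

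| 6-month window, μ = 0.5 | Phi 2.5 | Phi 1.75 |
|---|---|---|
| Power at N = 342 | 55.8% | 68.3% |
| Power at N = 429, all with full 6 months | 63.7% | 76.5% |
| N for 80% power | about 680 | about 476 |
| Rate ratio detectable with 80% power at N = 342 | 0.39 (61% reduction) | 0.47 (53% reduction) |

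**Step 3. Cross-check.** A two-group negative binomial Wald calculation with 114 per arm and k = 1.5 gives 79.8% at μ = 1.0 and 62.9% at μ = 0.5.

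**Step 4. Sensitivity to the missing rate.** If the 30% were entered as 0.3 falls per woman-year with Phi 2.5, N for 80% power would be about 1,133. Power at 342 would be 41% over 12 months and 27% over 6 months. Across other settings (one- or two-sided, other dummy shares, R² of 0 or 0.25), each calibrated to 80% over 12 months, halving the exposure with Phi fixed gives about 46% to 58%. None keeps 80%.

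**The case against.** The strongest reply is that the 12-month input is inferred. The exposure setting of the power run is not shown, the wording could denote an annualised rate, and the 47% effect came from tai chi programmes of 3 or 6 months. It is true that the run itself cannot be seen. But the section cites a 1-year fall figure, the study period is 12 months, and no 6-month expected count appears anywhere. The duration of the earlier programmes bears on the effect size, not on how many falls this trial will observe. If a 6-month count was in fact used, the printed horizon is wrong and still needs correcting.

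A second reply is that power should not be judged at 342 alone. The Data analysis plan analyses every randomized woman and adjusts dropouts for exposure time, so partial follow-up adds information. This stands: on a given Phi, the relevant power lies between the 342 and 429 values. Even the upper bound, which assumes no dropout, is below 80% at the assumed rate.

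Third, the size of the loss depends on a rate that the document does not give. This also stands. A reader might infer that the trial's true power is 56% to 68%, or that the sample-size arithmetic is wrong. The document supports neither: those percentages hold only under the assumed 1.0 fall per woman-year, and the printed 342 cannot be checked without the rate.

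**Conclusion.** The power statement and the primary test refer to different windows, and no section reconciles them. Read as written, the primary test does not have the stated 80% power for a 47% reduction. The direction of the loss follows from the shorter exposure at a constant fall rate and does not depend on which rate is assumed; its size does. At 1.0 fall per woman-year, two-sided alpha 0.05 and R² 0.25, 6-month power runs from 55.8% (342 women, Phi 2.5) to 76.5% (429 women with full exposure, Phi 1.75).

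A reader might also infer that making the 12-month count primary would restore 80%. The document does not support that. A 12-month count averages 6 months of supervised training with 6 months after it ends, and whether the benefit lasts is what the third aim asks. A 47% reduction may not hold over that period.

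**What to change.** Keep falls from baseline to 6 months as the primary count. In Power and sample size, state the control-group mean number of falls, the exposure time and the sidedness used in the power run. Then recalculate for 0 to 6 months, saying how Phi is taken to behave over the shorter window and how dropouts' partial exposure is counted. Restate the resulting power, or the reduction detectable with 80% power, there and in the abstract, so that both agree with Primary outcome and Data analysis plan. The figures above are a guide to what to expect; they should not be copied in unless the assumed rate of 1.0 is confirmed.

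The restatement needs no extra participants or visits. Its cost is a less favourable power figure in a prominent place. Switching the primary count to 12 months is not an equal alternative, because it changes the question being tested.

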Maximizing participant retention is a primary goal for conduct of the trial. Retention rates in prior exercise studies of similar length by the investigative team and in a similar population are strong (82%-85%).^21, 79^ and similar retention strategies are used for the GET FIT trial and include the following: 1) regular participant phone contact during the study 2) reserved parking place near the OHSU School of Nursing for testing appointments 3) free and close-in parking to exercise classes (as close as 200m for physically limited participants) 4) public transportation costs covered for participants who choose not to drive, 5) $10 remuneration at the end of each measurement appointment as a token of thanks, 6) allocation of every participant to an exercise program, including control group participants, 7) offering exercise classes at various community locations in the study area, and 8) encouragement of group cohesion by promoting social interaction through activities inside and outside of class (i.e., holiday potlucks, coffee/tea dates, team building activities during classes).

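### 143 per group does not protect 114 completers against 25% attrition: it leaves about 107 and covers losses only up to about 20%

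*Protocol article*

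**What the plan says.** Under Power and sample size, the protocol article states that "a sample size of n=342 (n=114 per group) will provide 80% power to detect at least a 47% reduction in the fall rate" over one year. It then adds the allowance for loss: "To protect against an estimated attrition of 25% during the intervention period, 143 participants will be randomized per group (total sample size: N=429"). It bases the 25% on yearlong weighted-vest studies in breast cancer survivors. It describes that rate as a little above the 19%-24% seen with tai chi and the 24% seen with resistance exercise in older women without cancer.

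The abstract (Methods/Design) repeats the pairing: "The sample for this trial (N=429, assuming 25% attrition) will provide adequate statistical power" for the 47% reduction.

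Two other places bear on the point. The Data analysis plan has each woman analysed as randomized and adjusts the fall rates of dropouts for their time in the study. The Discussion reports retention of 82%-85% in the team's earlier studies of similar length.

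**The concern.** The text gives three numbers that should fit together: the number needed (114), the loss expected (25%) and the number to randomize (143). A reader takes them to mean that about 114 per group remain if a quarter are lost. On the plan's own figures they do not.

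What is at stake is the tolerance for loss that the trial team and its monitors believe they have. The text says 25%, but the margin ends near 20%. The 24% that the same paragraph cites for resistance exercise, and the top of its tai chi range, would already take the trial below 114. The statement concerns the primary endpoint and appears in the abstract.

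**Working it through.** **Inputs.** From Power and sample size: 114 per group (342) required; power 80%; alpha 0.05, sidedness not given (two-sided assumed); attrition 25%; 143 per group (429) randomized in three equal groups. From the Data analysis plan: dropouts' exposure time is counted. From the Discussion: past retention 82%-85%.

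**1. Reproducing the stated 143.**
- Multiplying by (1 + loss): 114 × 1.25 = 142.5, rounded up to 143; 3 × 143 = 429. This matches.
- Dividing by (1 − loss): 114/0.75 = 152; 3 × 152 = 456. This does not match; the gap is 9 per group and 27 overall.
- Dividing with a 20% loss: 114/0.80 = 142.5, also 143. The number therefore fits a correct calculation at 20%, but the document says 25% in both places.

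**2. What 25% attrition leaves.**
- Per group: 143 × 0.75 = 107.25, against 114.
- In total: 429 × 0.75 = 321.75, about 322, against 342. The shortfall is about 20 women, or 6%.

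**3. Attrition that 143 can absorb.** 1 − 114/143 = 29/143 = 20.3%.

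| Attrition | Source | Left per group of 143 |
|---|---|---|
| 15% | team's 85% retention | 121.6 |
| 18% | team's 82% retention | 117.3 |
| 19% | low end, tai chi studies | 115.8 |
| 24% | high end, tai chi; resistance exercise | 108.7 |
| 25% | planning assumption | 107.25 |

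**4. Power if dropouts contribute nothing.** Scale the noncentrality from 80% at 114: power = Φ[(1.960 + 0.842) × √(n/114) − 1.960].
- n = 107: 2.802 × 0.9688 − 1.960 = 0.754, so power is 77.5%.
- With a one-sided alpha the result is 77.8%.

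This step needs no baseline fall rate. As a cross-check, take a Poisson-regression sample-size formula with the stated overdispersion of 2.5 and shared variance of 25%, one third of women in the exposed category, and a control rate of 1.0 fall per person-year. It gives 340 for 80% power, and power of 80.2% at 342 and 78.1% at 321.75. The rate of 1.0 is an assumption chosen because it comes close to 342. The article states neither a baseline rate nor the formula.

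**5. Allowing for dropouts' exposure.** Suppose information is proportional to exposure and dropouts contribute on average a fraction f of their follow-up. The effective number per group is then 143 × (0.75 + 0.25f) = 107.25 + 35.75f.
- Break-even with 114: f = 6.75/35.75 = 19%.
- f = 25% (dropout spread evenly over the 6-month intervention, on a 12-month horizon): 116.2.
- f = 50% (the same pattern on the 6-month analysis window): 125.1.

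The timing of dropout is not stated, so these values of f are illustrations.

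**The case against.** The strongest reply is that a dropout is not a zero. Falls are reported monthly, every woman is analysed as randomized, and the negative binomial model uses her time at risk. If dropouts supply about 19% of their follow-up on average, 143 per group carries the information of 114 full participants. Even spread of dropout over the intervention would exceed that. This stands as an argument about power. It does not rescue the sentence, because the power section presents 143 simply as 114 inflated for attrition and never invokes partial exposure. It also does not help the mediation analysis, whose baseline-to-6-month difference scores early dropouts cannot supply.

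A second reply is that the team has kept 82%-85% of participants, which would leave about 117 to 122 per group. That suggests 429 may well be enough in practice, but the planning assumption in the text is 25%.

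A reader might go further and infer that the trial is underpowered or must enrol 27 more women. The documents do not support that: the worst case is a loss of about 2.5 points, and it may be nil. Nor does the abstract flatly misstate the power. It promises adequate power rather than 80%, and about 78% does not plainly contradict that. The clear conflict lies within Power and sample size. Finally, that the authors multiplied by 1.25 is an inference: it fits exactly, but so does division at 20%.

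**Conclusion.** The point holds as a minor arithmetic correction. With 25% attrition, 143 randomized per group leaves about 107 (about 322 in total), not 114 (342). Protecting 114 against that loss takes 152 per group (456), and 143 protects only up to about 20%.

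The cost in power is at most about 2.5 points, from 80% to about 77.5%. This takes the plan's 80% at 114 as given, a two-sided alpha, and no data from dropouts. The loss disappears if dropouts contribute about 19% of follow-up on average, with information taken as proportional to exposure. The 107 and the 20% limit rest on the document's own figures alone.

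**What to change.** Preferred: keep the 25% and correct the consequence. Under Power and sample size, state that randomizing 429 leaves about 107 per group (about 322 in total) at 25% attrition, with about 77-78% power if dropouts contribute no data. Add that the exposure-adjusted analysis should recover some or all of the difference. Align the abstract's sentence. The cost is one sentence in each place, with no extra participants and no change to design or analysis.

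Alternative: state that 429 covers about 20% attrition, in both places. This costs a little more text, because the present justification argues for 25% and cites 19%-24% and 24%. It would have to be rewritten, for example around the team's own 82%-85% retention. Any baseline fall rate used to support a restated power should be labelled as an assumption.
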